### Voluntary exercise intervention group

Subjects randomized into the VE group will participate in 3 weekly exercise sessions over the course of 8 weeks for a total of 24 sessions. Exercise sessions will consist of a 5-minute warm up, a 40-minute main exercise set, and a 5-minute cool down on a standard stationary bicycle. All sessions will be completed under the guidance of an exercise physiologist. For participants who are deconditioned upon study enrollment, rest breaks will be allowed for 2 minutes every 10 minutes during the 40-minute main exercise set. Participants will be asked to pedal at a self-selected pace, and will be encouraged to achieve their target HR range, which will be calculated from their resting and maximal HR during the CPX test using the Karvonen formula at 60-80% of their max exertion [29]. HR, cadence, and power will be recorded every 5 minutes, and the rate of perceived exertion will be recorded every 10 minutes. Supervising exercise trainers and study personnel will be certified in Basic Cardiac Life Support. If a participant exhibits signs of cardiac distress or hemodynamic compromise, the exercise session will be stopped immediately and the on-call physician will be paged to the exercise laboratory. Following completion of the 24 session exercise intervention, participants will be instructed to resume pre-enrollment activity levels.

### Forced exercise intervention group

Participants in the FE group will receive a dose-matched intervention compared with the VE group. While our preliminary trials involved tandem cycling, in an attempt to make the intervention more feasible in a clinical setting, we have designed a stationary, motorized bike to augment self-selected cadence. The clear difference between the cycling groups is that while the VE group will use a standard stationary bike, participants in the FE group will be using a standard stationary bicycle that has been retrofitted with a motor to augment pedaling rate. In order to ensure that the participant is actively contributing to the pedaling motion, the algorithm used to control the assisted-cycle is responsive to pedal rate, the torque exerted on the pedals by the participant, and the torque produced by the motor during exercise. Based on our preliminary work with FE and PD, the cadence will be set at a rate that is approximately 30% greater than the individual’s self-selected pace during the CPX test [21]. It is important to note that although the participant will be cycling at an augmented rate, it is an active, not passive, activity. Power, cadence, HR, and rating of perceived exertion will be recorded at the same time intervals as the VE group.

### No exercise control group

Participants in the no-exercise control group will be instructed to maintain their pre-enrollment level of activity throughout the duration of their study enrollment. The study’s exercise physiologist will conduct weekly phone calls to ensure adherence, itemize participants’ activity levels, and monitor current medication regimes.

### Testing and outcome measures

Clinical tests, biomechanical tests, and MRI results will be compared at the following time points: baseline, midpoint, EOT, EOT + 4 weeks, and EOT + 8 weeks as depicted in Table 1. All testing will be completed in the ‘off med’ state, where the participant will be ask to abstain from their antiparkinsonian medication after 8pm the night preceding testing. The exception is baseline testing, which will be conducted over 2 days, one day in the ‘on med’ state and the other in the ‘off med’ state (randomized). The Research Electronic Data Capture (REDCap©) Database, a secure electronic database, will be used to record and store data.

**Table 1 Tab1:** **Summary of outcome measures**

**Assessment**	**Baseline***	**Baseline***	**Mid-point**	**EOT**	**EOT + 4 weeks**	**EOT + 8 weeks**
**Medication Status**	**On**	**Off**	**Off**	**Off**	**Off**	**Off**
UPDRS motor subscale	X	X	X	X	X	X
Beck Depression Inventory II		X		X		
University of Pennsylvania Smell Identification Test	X	X		X	X	
Timed Up and Go	X	X	X	X	X	X
Hopkins Verbal Learning Test	X	X	X	X	X	X
Parkinson’s Disease Questionnaire-39		X		X		
Trail Making Test	X	X	X	X	X	X
Simple & Choice Reaction Task	X	X	X	X	X	X
Processing Speed Test	X	X	X	X	X	X
Postural Sway	X	X	X	X	X	X
Nine Hole Peg Test	X	X	X	X	X	X
MRI	X	X		X	X	

* Baseline ‘on meds’ and ‘off meds’ are randomly assigned to be testing day 1 or 2.

Clinical and biomechanical measures will be used to assess motor and non-motor outcomes. The primary clinical motor outcome measure will be the UPDRS motor subscale, a well-studied test used to obtain a comprehensive clinical rating of PD [22]. The rater for this test will be blind to subject randomization. A secondary motor outcome will be the Timed Up and Go (TUG) is a reliable physical performance measure that assesses the time required for an individual to stand from a chair, ambulate 3 meters, turn 180 degrees, ambulate back to the chair, and return to a seated position [30].

Other clinical non-motor assessments will include the Parkinson’s Disease Questionnaire-39 (PDQ-39), University of Pennsylvania Smell Identification Test (UPSIT), Hopkins Verbal Learning Test, and the Beck Depression Inventory II (BDI-II). The PDQ-39 is a 39-item questionnaire that assesses the quality of life in individuals with PD [31]. In the UPSIT, which is used to assess hyposmia, the participant is asked to identify 40 odorants presented on microencapsulated booklet [32]. The Hopkins Verbal Learning Test is used to assess verbal memory of the participant [33], and the BDI- II questionnaire assesses depressive symptomology [34].

In an effort to gather biomechanical outcomes, several novel electronic mobile applications will be utilized. The modules, developed on the Apple iPad, include the Trail Making Test, Simple Reaction Task, Choice Reaction Task, Processing Speed Test, and a measure of postural sway in standing. The utilization of the iPad modules to assess cognitive and motor function provides a method of obtaining biomechanical data in a cost and time efficient manner compared to traditional biomechanical measures. Briefly, the Trail Making Test module is based on a widely-used neuropsychological assessment designed to evaluate executive function that involves connecting numbers (1-2-3…) and a number/letter sequence (1-A-2-B….) that are arranged on paper [35]. In the case of the app, the targets are arranged in a similar manner while using Fitts’ Law to ensure the segment of difficulty is matched across the paper and pencil form compared to the iPad version [36]. The electronic version administered on the iPad samples the time and X-Y position data at 60Hz which is then used to determine when the patient is moving versus searching for the next target [37]. The Simple Reaction Task module provides quantitative data on information processing by measuring the time between the presentation of a stimulus and the participant’s response [37]. The Choice Reaction Task module measures reaction time with more complex thinking, as one of two stimuli is randomly activated and the participant is timed from presentation to selection of the stimuli [37]. The technology of the iPad allows the reaction time speed to be measured accurately to the millisecond. The Processing Speed Test module is a modified, electronic version of the paper-and-pencil symbol-digit matching test which assesses complex attention and information processing speed [38,39]. For the module, the participant is presented with nine symbols matched with Arabic numerals 1-9. Below the key, symbols alone are presented to the participant. The participant is asked to correctly match as many symbols as possible to the corresponding numeral in 90 seconds.

As a biomechanical measure of balance, the gyroscope and accelerometer of the iPad will measure volume of postural sway [37,40-43]. We have validated the use of the iPad to characterize balance in young, healthy older adults, and individuals with PD [37,40-43]. Attached to the waist of the participant, the iPad captures linear and rotational movement to calculate the volume of postural sway (Figure 2). The postural sway test consists of a 30-second trial on the following conditions: 1) firm surface, double leg stance, eyes open; 2) firm surface, double leg stance, eyes closed.

**Figure 2 Fig2:**
[figure not shown]
The iPad’s gyroscope and accelerometer capture linear and rotational movement to calculate volume of postural sway when belted to the waist of the participant. In this figure, the iPad is counting down from 30 seconds as the participant performs the following stances: 1) double leg stance, firm surface, eyes open; 2) double leg stance, firm surface, eyes closed.

The Nine Hole Peg Test (NHPT) will be used as a measure of manual dexterity [44]. Consistent with our effort to objectify our outcome measures, the NHPT module is an electronic form of the traditional NHPT (Figure 3). Participants are instructed to pick up individual pegs from a dish, place them in the nine peg slots until all slots are filled, and then remove the pegs. The electronic version is an overlay mold over the iPad and has been shown to be reliable in individuals with multiple sclerosis [39]. The iPad capacitive touch screen detects the time between each peg insertion and removal, which provides a more precise temporal-spatial understanding of manual dexterity than the traditional measure.

**Figure 3 Fig3:**
[figure not shown]
A transparent plastic overlay attaches to the iPad to create the electronic version of the NHPT. The participant performs the first segment of the NHPT by transferring the pegs from a dish to one of the 9 holes, removing the pegs, and returning them to the dish, which is measure of in-hand manipulation and manual dexterity. The second part of the test involves transferring pegs to and from a row (pictured on the right of the iPad screen below) rather than the dish to calculate transport time only. The capabilities of the iPad allows for detection of the time between each peg insertion and removal.

### MRI data collection

For this study, structural MRI, functional MRI (fMRI), fcMRI and cerebral blood flow (CBF) data will be acquired on four occasions: Baseline (on and off antiparkinsonian medication), EOT, and EOT + 4 weeks. The structural scan is a T1-weighted anatomic image for identifying brain anatomy. The fMRI and fcMRI scans will be acquired with blood oxygen level-dependent (BOLD)-weighted echoplanar imaging scans. Two fcMRI scans will be acquired while subjects rest in the scanner with eyes closed. Two fMRI scans will be acquired in each session while subjects complete finger tapping in the following self-paced repeating sequence: digit 1, digit 3, digit 5, digit 2, digit 4 with each limb (left and right limbs, in random order) in a block paradigm (alternating 48 second-long blocks of tap and rest phases, repeated 4.5 times) to determine the relationship between changes in upper extremity motor performance and pattern of brain activation. Additional measures recorded for exploratory purposes include fcMRI between nodes of the putative motor network.

### Data analysis

Participants in all three groups will be compared descriptively on potentially confounding baseline variables (i.e., age, disease severity, and levodopa equivalent daily dose (LEDD)) to assess the extent of any imbalance across groups. Baseline variables in which there appears to be a clinically important baseline difference, or in which the standardized difference (absolute value of difference in means divided by pooled SD) between any 2 groups is greater than 10% will be included as covariates. P-values from these baseline variable comparisons will not be used to determine the need for covariate adjustment, as that criterion can be misleading.

The FE, VE, and the no-exercise control groups will be compared on each outcome of interest (motor, non-motor) using repeated measures analysis of covariance. For motor and non-motor outcomes, groups will be compared on outcomes at the mid-treatment, EOT, EOT + 4 weeks, and EOT + 8 weeks adjusting for the baseline (on and off medication) period as a covariate. The effects of group, time, and the group-by-time interaction will be assessed for each outcome. In the case of a significant interaction, the groups will be compared at each time point. Tukey’s correction for multiple comparisons will be used. Data will be transformed as needed to meet model assumptions. In addition to p-values, the estimated treatment effect and its 95% CI will be of interest as these data will aid in formulating exercise recommendations and potential benefits. For each hypothesis, significance level will be set at 0.05. Each participant’s change in fitness based on change in peak VO_2_ from CPX testing will be used as a covariate. This will remove the effect of possible differences in improvement in fitness level across the groups from confounding the results. Correlation between LEDD and the time spent within target HR zone during training, amount of work performed, and change in primary outcome variables in motor and non-motor outcomes will be assessed. If the LEDD is significantly correlated with these outcomes, it will be included as a covariate in the related analysis.

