## Methods and design

### Study design

This single center, prospective, rater-blind, three arm clinical trial will investigate the efficacy of a FE paradigm on motor and non-motor symptoms in individuals with PD. A total of 100 individuals with mild to moderate idiopathic PD will be enrolled. CYCLE Trial protocol is approved by the Cleveland Clinic Institutional Review Board and all participants will sign an informed consent prior to beginning the study. Written informed consent was obtained for any photographs that have been taken for publication. A schematic overview of the enrollment, testing, and intervention is shown in Figure 1.

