### Randomization

Participants will be randomized 2:2:1 into FE, VE, or no-exercise control group. The uneven allocation of subjects was selected due to the promising results of the preliminary data by [name], et al. indicating there is a benefit to cardiovascular exercise that would not been seen in a control group [20,21]. Enrollment will total 18 weeks: two weeks allotted for baseline evaluations, 8 weeks of exercise intervention or control period, and 8 weeks for a follow up period in which the participant is instructed to return to their baseline level of physical activity.

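### The covariate set is not fixed in advance: the 10% imbalance rule fires by chance about 92% of the time per variable, and LEDD has a second, outcome-driven route into the model

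*Protocol article*

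**What the plan says.** All of this is in the Data analysis section of the protocol article.

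- **Imbalance rule (first paragraph).** The candidates, given as examples of potential confounders, are age, disease severity and LEDD. A candidate is added to the model if a difference seems clinically important, or on the size of its standardized difference, which is the absolute gap between two group means over the pooled SD. Variables in which this quantity "between any 2 groups is greater than 10% will be included as covariates".
- **Bar on P-values (end of the first paragraph).** "P-values from these baseline variable comparisons will not be used to determine the need for covariate adjustment, as that criterion can be misleading".
- **LEDD rule (end of the second paragraph).** LEDD is to be correlated with time in the target heart-rate zone during training, with the work performed, and with change in the primary motor and non-motor outcome variables. Then: "If the LEDD is significantly correlated with these outcomes, it will be included as a covariate in the related analysis".
- **Already fixed.** The outcome's own baseline, on and off medication, is a covariate unconditionally.

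The arm sizes follow from two other statements: "A total of 100 individuals with mild to moderate idiopathic PD will be enrolled" (Study design) and "Participants will be randomized 2:2:1 into FE, VE, or no-exercise control group" (Randomization), which give 40, 40 and 20.

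**The concern.** A 10% threshold applied to three pairwise comparisons, two of which involve an arm of only 20, is small compared with the chance variation in those differences. A rule that fires on noise does not identify confounding. It makes the covariate list a matter of luck, and the alternative route through apparent clinical importance rests on judgement exercised with the group data in view.

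The LEDD rule raises a different problem. Its inputs include the change in the outcome to be analysed, so the analysis model for that outcome can depend on the outcome data. It is applied per related analysis, so the covariates may differ between outcomes. Two of its three inputs, time in the heart-rate zone and work performed, come from training sessions that the control arm does not have (No exercise control group). The text also does not say whether one significant correlation is enough or all are needed.

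At stake is whether the model for the primary outcome, the UPDRS motor score, is fixed before anyone has seen the results.

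**Working it through.** **Inputs.** Arms of 40/40/20 (N = 100, 2:2:1); threshold 0.10 on |difference in means| / pooled SD; three pairs, any one sufficient; three candidate variables. The article states no firing rate for its rule, so there is no figure of its own to reproduce. Assumptions: a continuous, roughly normal covariate, simple randomization and no true imbalance.

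**Step 1: each pair.** The standardized difference has standard error √(1/n₁ + 1/n₂), and the chance of exceeding 0.10 is 2[1 − Φ(0.10/SE)].

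| Pair | SE | 0.10/SE | Chance of exceeding 0.10 |
|---|---|---|---|
| Forced vs voluntary (40, 40) | 0.2236 | 0.447 | 65.5% |
| Either exercise arm vs control (40, 20) | 0.2739 | 0.365 | 71.5% |

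**Step 2: any of the three pairs.** The pairs share arms and are correlated, so this was simulated (400,000 trials). The result is 91.8% with the SD pooled over all groups and 91.9% with pairwise SDs. With 10% fewer participants analysed (36/36/18) it is 92.7%, and with 20% fewer (32/32/16) it is 93.4–93.5%. If severity were a two-level stage instead of a continuous score, the rate is 88–94%.

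**Step 3: a higher threshold.** At 40/40/20 the chance rate per variable is 71% at 0.20, 59% at 0.25 and 13–14% at 0.50. Raising the cut-off to 0.20 or 0.25 would still leave a rule that mostly responds to chance.

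**Step 4: three variables, treated as independent, imbalance rule alone.** With a rate of 0.9185:

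- at least one fires: 1 − (1 − 0.9185)³ = 99.9%
- all three fire: 0.9185³ = 77.5%
- at least one is left out: 1 − 0.775 = 22.5%, about 23%

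**Step 5: with the LEDD route added.** Null trials were simulated with a three-group analysis of covariance on a single follow-up outcome (6,000 trials per row). LEDD was also admitted if it correlated with the outcome at P < 0.05. The coefficient is that of each of the three covariates, in units of the residual SD.

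| Coefficient | At least one of the three left out | Type I error, imbalance rule | LEDD rule only | Both rules | Fixed set of three |
|---|---|---|---|---|---|
| 0 | 22.2% | 5.3% | 5.2% | 5.3% | 5.3% |
| 0.3 | 17.4% | 4.7% | 5.2% | 4.8% | 4.9% |
| 0.5 | 16.1% | 4.1% | 5.0% | 4.3% | 4.9% |

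The Monte Carlo standard error at 5% is √(0.05 × 0.95/6,000) = 0.28 percentage points. No row shows inflation beyond that noise. Where the covariates are strongly prognostic, the imbalance rule is if anything slightly conservative.

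**Step 6: how often the LEDD route can matter.** Each rule ends in inclusion, so the literal reading is that either suffices. The correlation then changes the model for a given outcome only when LEDD has not already entered through imbalance, which is at most about 1 − 0.918 = 8% of trials. The two rules can still point in different directions (balanced but correlated, or imbalanced but uncorrelated), and the text does not say outright which governs LEDD.

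**The case against.** The strongest reply is that the rules do little harm. The 10% rule uses baseline data only, so it can be applied before any outcome is seen. Because it fires so often, it comes close to adjusting for everything, which is nearly what is recommended here. The outcome's own baseline is always in the model, and the documents give no figure for what age, severity and LEDD add beyond it. All of that stands, and it limits the point to how the model is specified.

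Three stronger readings are tempting, and none is supported.

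- **That the LEDD rule breaks the plan's own ban on P-values.** The ban covers P-values from between-group comparisons of baseline variables, and it closes a different paragraph. A correlation of LEDD with training measures and outcome change is another test. The rule sits badly with the reason given for the ban, since significance again decides adjustment, but it does not contradict the sentence.
- **That the whole primary model is settled only once outcomes are known.** Only the LEDD route uses outcomes, and on the literal reading it can alter the model in at most about 8% of trials.
- **That P-values become unreliable, or that a fixed set brings a material gain in precision.** The simulated type I error stays between 4.1% and 5.3%, and precision under the stated rules is nearly the same as with fixed covariates.

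The reply does not defend the rules themselves. A threshold that chance crosses nine times in ten serves no purpose as a filter, and letting outcome data choose a covariate is avoidable at almost no cost.

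**Conclusion.** The concern holds as a matter of prespecification. The 10% rule fires by chance about 92% of the time per continuous variable (88–94% for a two-level severity stage). At least one of the three named variables would still be left out in about 16–23% of trials. LEDD has a second, significance-based route that depends on the outcome when LEDD is balanced, can differ between outcomes, and uses two measures that do not exist in the control arm.

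These figures assume arms of 40/40/20, simple randomization, no true imbalance and, for the three-variable results, independence. The article describes no stratification and does not say how disease severity is measured. The error-rate simulation used one follow-up time, not the full repeated-measures model.

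The benefit of changing the text is a primary model free of outcome-dependent and subjective choice. It is not a correction of a faulty error rate. The change is worth making because it is almost free; the trial's validity does not hang on it.

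**What to change.** Delete both selection rules, including the route through apparent clinical importance. State instead that every motor and non-motor model includes age, baseline disease severity and baseline LEDD, together with the on- and off-medication baseline already specified, whatever the observed imbalance or correlation. Name the measure of disease severity. Report baseline differences between groups descriptively only. Keep the correlations of LEDD with training measures and outcome change as exploratory analyses with no bearing on the model, and say that the two training measures apply to the exercise arms only.

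The cost is wording, plus at most about 3 of the 97 (100 − 3) residual degrees of freedom. The stated rules would spend most of these anyway. The plan already uses all three variables, so no new data are needed.

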### Power analysis

For Aim 1, the UPDRS motor score will be the primary outcome. Our power analysis was calculated based on UPDRS motor data from our previous project comparing FE and VE interventions on UPDRS ratings. We observed a mean (95% confidence interval (CI)) reduction of -5.3 (-18.0, 7.4) in the FE group and 0.4 (-15.3, 16.1) in the VE group from baseline to end of treatment (EOT) at 8 weeks. This corresponds to a difference (improvement, reduction) in means (95% CI) of -4.9 (-20.6, 10.8), standard deviation (SD) of difference = 8.0, P = 0.004. Assuming similar variability for the current proposal, with N = 40 subjects per exercise group, we will be able to detect differences of 5.0 or more between groups on UPDRS with 90% power at the 0.05 significance level, adjusting for 3 group comparisons at each of EOT evaluations. No published data exists for outcomes in Aim 2 or 3 with respect to exercise and PD. In general, with 40 subjects per exercise group, power will be 99 percent to detect differences of 1.2 SDs or more between the groups. For Aims 1-2, comparisons at particular time points power is 90% to detect differences of 1.3 SD, applying a Bonferroni correction for analyzing time points (2 post-intervention times) individually. All calculations assume Tukey adjustment for comparing the 3 groups.

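### The trial is sized on the FE versus VE change to EOT, but group comparisons at single visits follow only a significant interaction, so the data decide whether an EOT difference or a four-visit average is tested

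*Protocol article*

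**What the plan says.** The Power analysis section names the outcome: "For Aim 1, the UPDRS motor score will be the primary outcome". Its planning data are FE and VE changes "from baseline to end of treatment (EOT) at 8 weeks". It then claims "we will be able to detect differences of 5.0 or more between groups on UPDRS with 90% power at the 0.05 significance level". That calculation takes 40 per exercise group, three between-group comparisons at the EOT evaluations, and Tukey adjustment over the three groups.

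The Data analysis section uses baseline as a covariate. The repeated outcomes are therefore the four later visits: mid-treatment, EOT, EOT+4 weeks and EOT+8 weeks. Group, time and group-by-time effects are assessed for each outcome, and then: "In the case of a significant interaction, the groups will be compared at each time point". It does not say what is done about EOT when the interaction is not significant.

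The Randomization section describes what lies behind the last two visits: "8 weeks for a follow up period in which the participant is instructed to return to their baseline level of physical activity".

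**The concern.** The interaction test asks whether group differences change across visits. It does not ask whether FE differs from VE at EOT. Because baseline is outside the time factor, a benefit that is present by mid-point and stays put produces no interaction, and the plan then offers no EOT comparison. If the benefit builds and fades, the interaction may or may not reach significance. When it does not, the remaining group test is the main effect, which averages one mid-training visit, EOT and two visits after training has stopped.

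Two trials with the same true EOT difference could therefore report different quantities, chosen by a p-value. The one reported need not be the one on which the sample size rests. The four-visit average also mixes effect during training with retention afterwards, which are separate clinical questions.

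**Working it through.** **Inputs from the protocol.** Difference 5.0, SD 8.0, 40 per exercise group, alpha 0.05 (taken as two-sided) and Tukey for three groups, all from Power analysis. Twenty controls follow from N = 100 and 2:2:1 allocation. The four visits come from Data analysis.

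**Assumptions not in the protocol.** SD 8 at every visit; compound symmetry with correlation 0.5-0.7 (0.4-0.8 where marked); VE equal to control; no baseline covariate; no dropout; effect profiles as listed. If the interaction is not significant, the group main effect is taken as the test.

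**Step 1: the plan's own figure.** Standard error of FE minus VE at EOT = 8 × √(1/40 + 1/40) = 1.789. Noncentrality = 5.0/1.789 = 2.795. The Tukey critical value (3 groups, 97 df) is 2.380, which gives power of 66%. Without adjustment, power is about 80%. The stated 90% is not reproduced at SD 8.0. That is a separate matter; here 66% is the benchmark for a direct EOT test.

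**Step 2: what the average estimates.** Each profile below has a true difference of 5.0 at EOT.

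- Constant: (5 + 5 + 5 + 5)/4 = 5.0
- 2.5, 5, 3.75, 2.5: 13.75/4 = 3.4
- 2.5, 5, 3, 1.5: 12/4 = 3.0
- 2.5, 5, 2.5, 0: 10/4 = 2.5
- 2.5, 5, 0, 0: 7.5/4 = 1.9

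The average has a smaller SD, 8 × √((1 + 3ρ)/4). This is 6.32 at ρ = 0.5 and 7.04 at ρ = 0.7, giving standard errors of 1.41 and 1.57 against 1.789 at EOT. Averaging therefore gains precision but loses signal when the effect fades.

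**Step 3: the procedure as a whole.** In simulation, FE versus VE is tested at EOT with Tukey if the interaction is significant at 0.05, and otherwise by the Tukey-adjusted main effect. With 4,000 trials per scenario the Monte Carlo standard error is about √(0.55 × 0.45/4000) = 0.8 points, so repeat runs differ by a point or so.

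| Profile (mid, EOT, +4, +8) | Interaction significant | Whole procedure declares FE vs VE | Direct EOT test |
|---|---|---|---|
| 5, 5, 5, 5 | about 5% | 79-86% | about 66% |
| 2.5, 5, 3.75, 2.5 | 18-51% (ρ 0.4-0.8) | 55-59% | about 66% |
| 2.5, 5, 3, 1.5 | 31-51% | 54-55% | about 65% |
| 2.5, 5, 2.5, 0 | 49-97% (ρ 0.4-0.8) | 56-64% | about 66% |
| 2.5, 5, 0, 0 | 66% to near 100% (ρ 0.4-0.8) | 60-65% | about 66% |

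Across the fading profiles the procedure loses between almost nothing and about 11 or 12 points against the direct test. With a constant effect it gains about 13 to 20 points.

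**The case against.** **The text may foresee an EOT comparison anyway.** Just before the conditional sentence, Data analysis says that groups will be compared at the four visits. It also says that estimates with confidence intervals are of interest. Power analysis budgets for three group comparisons at EOT evaluations and for time points analysed individually. This shows that visit-level comparison was in mind. But the only rule given for when it happens is the interaction result, and no visit is named for the estimates. At best the text is ambiguous about the primary test.

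**EOT is not declared the primary visit.** A reader might infer that a declared primary EOT test is being displaced. The protocol does not support that. It names UPDRS motor as primary without a visit, and Aim 1 gives no time point. EOT is inferred from the planning data. What stands is the mismatch between the powered contrast and the stated testing order.

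**The sequence is conventional, and the article is condensed.** Both are true, and a separate analysis plan may settle the matter. But the article does not leave the order open. It states one that does not fit its own power paragraph.

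**The gate need not cost power.** A reader might take the chance that EOT is both tested and significant (25-39% for the 2.5, 5, 3, 1.5 profile) as the plan's power and set it against about 65%. That leaves out the main effect as fallback; the plan's power for that profile is 54-55%. Under a constant effect the plan beats a direct EOT test. This objection stands in full.

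**Conclusion.** The point holds as a mismatch and as a data-dependent estimand. The sample size rests on FE versus VE change to EOT, while the stated testing order lets the interaction p-value choose between that difference and a four-visit average that includes two post-training visits.

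Its clearest size is in what is estimated: a true 5.0 at EOT becomes about 1.9 to 3.4 in the average under the fading profiles. The effect on power is modest and runs both ways: about 54-65% against 65-66% when the effect fades, and 79-86% against about 66% when it persists unchanged. The protocol does not support a general claim that the gate lowers power.

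The percentages depend on the assumed profiles, correlations, SD of 8 at each visit and absence of covariate adjustment. The mismatch itself depends on none of these, nor on the stated 90% power.

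**What to change.** State in Data analysis that the primary test is FE minus VE in UPDRS motor score, off medication, at EOT. Estimate it from the same repeated measures ANCOVA with Tukey adjustment, and test it whatever the interaction result. Report FE versus control and VE versus control at EOT in the same way. Make the interaction, the main effect and the other visits secondary.

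This takes about two sentences and no new data, and should be settled before any unblinded analysis. The price is some power relative to the averaged main effect if the benefit fully persists after training: about 66% instead of 79-86% under the assumptions above. If the investigators would rather have the four-visit average as the primary quantity, they should say so and base the power calculation on it.
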